### Data Analysis and Handling Missing Data

The analysis involves the use of advanced data management and statistical analysis software (eg, SPSS Statistics [IBM Corp] and Amos [IBM Corp]), and comparisons will be made between intervention groups using parametric statistical tests (eg, *t* tests and longitudinal or comparative analyses with repeated measures to determine participants’ progression). Initially, descriptive analyses of participants’ characteristics will be conducted, and the associations among research variables will be statistically analyzed (eg, Pearson correlations, partial correlations tailored to preliminary analyses, and group differences). We will use a method of controlling for additional variables that may influence statistical outcomes (eg, personal, medical, social, and demographic data) based on the results of the preliminary analyses.

The primary analysis (eg, participant randomization) will be based on the intention-to-treat principle. Missing data will be imputed using various techniques, and sensitivity calculations will compare the results to per-protocol analyses to determine the effect of dropouts.

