**Methods:**

A single-blinded randomized controlled trial will be conducted with 60 participants (n=30, 50% per intervention group) recruited from university and preuniversity counseling centers. The trial will measure whether the interventions reduce performance anxiety in students. Stratified randomization will be used to ensure equal distribution of baseline anxiety levels and gender across both groups. The primary outcome is a reduction in anxiety, measured using the State-Trait Anxiety Inventory-Y1 and State-Trait Anxiety Inventory-Y2 subscales. Secondary outcomes include emotional regulation and quality of life. Data will be collected at baseline, after the intervention, and during follow-up assessments. Statistical analyses will include parametric tests (eg, repeated-measures ANOVA and *t* tests) to compare anxiety reduction, emotional regulation, and quality of life across groups. The intention-to-treat approach will be applied to minimize bias due to participant dropouts. Sensitivity analyses will assess the robustness of the findings.

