### Participant Recruitment

Participants will be selected voluntarily. They will be invited to participate in the study through referrals from psychologists and psychiatrists working with individuals on waiting lists at counseling and mental health centers. These include psychological counseling centers at universities and preuniversity institutions. Eligible participants will be identified from the waiting lists of online platforms where they registered for counseling or psychotherapy related to emotional difficulties. Once identified, they will receive an invitation to participate in the research project. After expressing their intent to participate, each participant will receive an informed consent form detailing the study’s specifics. Participants will be formally included in the study upon signing the consent form. Finally, participants will be randomly assigned to one of the proposed psychoemotional support groups. This allocation will be conducted through random assignment, ensuring balanced groups in terms of financial level, type of education, and clinical level of anxiety.

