### Procedure

#### Overview

Participants will be invited to attend one of the psychoemotional support groups where they will benefit from either VR-facilitated exposure techniques based on cognitive behavioral intervention modalities or techniques based on the combination of postures (asana), breathing (pranayama), and meditation. Before allocation to the psychoemotional support conditions, each participant will be assessed using a personal data sheet to consider relevant medical, social, and demographic data and exclusion criteria.

This study will use a comprehensive set of preassessment measures to ensure stratified randomization before group allocation. First, measures of both state and trait anxiety are used to ensure participants are grouped appropriately according to their baseline anxiety levels before intervention allocation. Levels of clinical anxiety and emotional regulation mechanisms relevant to anxiety management as well as specific manifestations of performance anxiety will be assessed before the start of the intervention program. Randomization into groups will be done after the initial assessment and will consider an equitable distribution, and the equitable distribution will be considered according to anxiety levels. Given the impact of baseline anxiety levels on treatment effectiveness, a stratified randomization technique is used. This protocol outlines that participants are first stratified based on their anxiety scores and gender before being randomized into the 2 intervention groups. Stratification ensures that individuals with high-trait anxiety and low-trait anxiety are evenly distributed across both treatment groups. Similarly, gender will be controlled to ensure that results are not confounded by gender-related emotional regulation tendencies. This type of stratification minimizes variance and ensures comparable starting conditions for both groups. Finally, this process controls for preexisting differences, leading to stronger statistical effects.

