### Sample Size Determination

Considering that the research aims to test and compare 2 types of interventions (VR-facilitated exposure and yoga techniques), using a small sample population allows a detailed initial analysis and a rigorous evaluation of the mechanisms involved without requiring significant resources or large samples. In the exploratory phase, this type of study can identify important preliminary trends and effects, which can later be validated through larger studies. The study involves continuous monitoring of anxiety and other psychological and neurobiological parameters, which requires considerable resources for each participant. A small sample enables closer and more detailed tracking of each participant, ensuring higher-quality data collection and avoiding uncontrolled variables. The proposed interventions, such as yoga techniques and VR exposure, are complex and require specific preparation for each participant. Thus, a smaller population allows for more efficient adaptation of the intervention to individual needs and optimal program implementation. In addition, studies of this type often require costly equipment and expertise, such as VR hardware and certified yoga instructors. Therefore, limiting the sample population allows for efficient use of available resources while maintaining intervention quality. Finally, it is worth noting that previous studies have shown that both yoga and VR interventions can yield significant results with a limited number of sessions and participants. This suggests that a small sample may be sufficient to detect the desired psychological effects in the initial phase. Considering power analysis, 30 participants per group are required to detect significant differences regarding anxiety reduction with 80% power at a 5% significance level.

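### Covariates come from preliminary results, baseline STAI and the stratification factors are not named as covariates, and the allocation factors are stated two ways: an avoidable loss of power

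*Protocol article*

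**What the plan says.** **Analysis.** Under Data Analysis and Handling Missing Data, "comparisons will be made between intervention groups using parametric statistical tests", with t tests and repeated-measures analyses as the examples. The Abstract (Methods) likewise names repeated-measures ANOVA and t tests. The only adjustment described is "controlling for additional variables that may influence statistical outcomes (eg, personal, medical, social, and demographic data) based on the results of the preliminary analyses". The same paragraph describes the preliminary work as correlations, partial correlations and group differences in the trial data.

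**Outcome and size.** "The primary outcome is a reduction in anxiety, measured using the State-Trait Anxiety Inventory-Y1 and State-Trait Anxiety Inventory-Y2 subscales". The Abstract gives "60 participants (n=30, 50% per intervention group"), and Sample Size Determination says "30 participants per group are required to detect significant differences regarding anxiety reduction with 80% power at a 5% significance level".

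**Allocation.** Procedure, Overview: "participants are first stratified based on their anxiety scores and gender before being randomized into the 2 intervention groups". That section justifies this by the influence of baseline anxiety on treatment effect, and claims lower variance and stronger statistical effects in return. The Abstract and Research Design also name baseline anxiety and gender. Participant Recruitment instead describes random assignment "ensuring balanced groups in terms of financial level, type of education, and clinical level of anxiety"; gender is absent.

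**The concern.** Three statements do not fit together.

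1. Stratifying on a prognostic variable makes the arms more alike, but the standard error shrinks only if the analysis conditions on that variable. The protocol claims the gain and then names tests that do not take it.
2. The only adjustment it commits to depends on what the trial's own data show. The candidate pool under Instruments, Overview is wide (education, finances, marital status, profession, medical data and more), and neither a selection rule nor a primary model is given. An analysis plan that fixed the covariates would contradict this sentence.
3. The allocation factors differ between sections, so it is unclear which factors an adjusted model should contain.

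At stake are power in a 60-person trial, and a reader's confidence that the reported model was not picked for its result.

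**Working it through.** **The plan's own figure.** No effect size or SD is given for the 30 per group, so it can only be back-solved. With two-sided 5% (sidedness is not stated; assumed) and 80% power, the normal approximation gives d = (1.960 + 0.842) × √(2/30) = 0.72. The t test gives 0.736. The 30 per group is therefore neither confirmed nor refuted.

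**Assumptions.** n = 30 per arm, no dropout, one post-intervention score, baseline-outcome correlation ρ of 0.3 to 0.7, and d of 0.5 or 0.736. The documents give neither ρ nor d.

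**Variance of the arm comparison, relative to the post-score test (= 1).**
- Change score, which equals the group-by-time test in a two-time repeated-measures ANOVA: 2(1 − ρ)
- ANCOVA on baseline: 1 − ρ²
- ANCOVA against change score: (1 − ρ²) / [2(1 − ρ)] = (1 + ρ)/2, which is 0.65, 0.75 and 0.85 at ρ = 0.3, 0.5 and 0.7

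At ρ = 0.5 the ratio of 0.75 is equivalent to 1/0.75 = 1.33 times the participants. This holds at that correlation only.

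**Power (noncentral t, 58 df).** The effective effect is d for the post score, d/√[2(1 − ρ)] for change and d/√(1 − ρ²) for ANCOVA. Example with d = 0.5 and ρ = 0.5: 0.500, 0.500 and 0.577.

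| d | ρ | Post score | Change score | ANCOVA |
|---|---|---|---|---|
| 0.5 | 0.3 | 48% | 36% | 52% |
| 0.5 | 0.5 | 48% | 48% | 59% |
| 0.5 | 0.7 | 48% | 69% | 76% |
| 0.736 | 0.3 | 80% | 66% | 84% |
| 0.736 | 0.5 | 80% | 80% | 90% |
| 0.736 | 0.7 | 80% | 95% | 97.5% |

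**Type I error under stratified allocation.** 10,000 simulated trials of 60 per setting, stratified on median-split baseline and gender, with gender having no effect on outcome and nominal 5%. ANCOVA contains arm, baseline and gender.

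| ρ | Post score | Change score | ANCOVA |
|---|---|---|---|
| 0.3 | 4.4% | 2.6% | 5.1% |
| 0.5 | 3.3% | 3.1% | 4.7% |
| 0.7 | 2.0% | 3.7% | 4.9% |

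A separate run of 5,000 gave 3.3%, 3.4% and 5.2% at ρ = 0.5, and 1.8%, 4.0% and 5.2% at ρ = 0.7. The unadjusted tests are conservative. Simulated power at d = 0.5 agrees with the formula: 48%, 48% and 59% at ρ = 0.5; 47%, 70% and 75% at ρ = 0.7.

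**Covariates chosen from results.** 5,000 null trials with 10 covariates unrelated to outcome, added to the post-score test:

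| Rule | ρ = 0.5 | ρ = 0.7 |
|---|---|---|
| Post-score test, no selection | 3.3% | 1.8% |
| Add those correlated with outcome (p < 0.05) | 3.2% | 2.0% |
| Add those imbalanced between arms (p < 0.05) | 3.1% | 2.1% |
| Smallest p of 11 models (none, or one covariate) | 5.8% | 3.5% |
| Smallest p of post score, change, ANCOVA | 6.6% | 6.5% |

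A rule fixed in advance does not inflate the error. Picking the model by its p value raises it, and in three of the four cases takes it above 5%.

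**Allocation factors side by side.** Abstract, Research Design and Procedure: anxiety and gender. Participant Recruitment: finances, education type and clinical anxiety level. Only anxiety is common to both lists. Its description also varies: anxiety scores and high or low trait anxiety in Procedure, clinical level in Recruitment.

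**The case against.** **The model is for the analysis plan to specify.** The methods are introduced as examples, and an article may leave the full model to another document. This stands for mere silence about covariates. It does not cover the sentence that ties adjustment to preliminary results, nor the conflict between the two lists, both of which are affirmative text.

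**Baseline is not ignored.** A reader might infer that baseline STAI drops out of the analysis. The documents do not support that: data are collected at baseline, and repeated-measures ANOVA carries it as a time point. What is missing is its use as a covariate, and against the change score the loss is small when ρ is high (95% against 97.5% at d = 0.736, ρ = 0.7).

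**No inflated error is shown.** A reader might infer that data-driven covariates raise the false-positive rate. That needs the model to be picked by its result, which no section proposes. The Blinding section also keeps analysts unaware of assignment. Blinding limits steering towards one arm, but a p value can be seen without arm labels, so the risk is reduced, not removed.

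**The list can be built.** A reader might infer that the randomisation list cannot be made, or that all the factors would be crossed into nearly empty cells. Three sections agree on anxiety and gender, Participant Recruitment does not call its factors strata, and nothing proposes merging the lists. It is a conflict to reconcile, no more.

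**Stratum and continuous baseline overlap.** They do for the subscale used to stratify, but the cost is negligible: in the simulation at d = 0.5 and ρ = 0.5, ANCOVA had 59.3% power without the anxiety stratum and 58.8% with it.

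**Conclusion.** The point holds as an inexpensive improvement in efficiency and prespecification, not as a demonstrated error in the conclusions the trial would reach. The stated tests do not use the stratification from which the protocol claims a gain. They are conservative (about 2 to 4.5% at nominal 5% for ρ of 0.3 to 0.7) and lose power against ANCOVA: roughly 11 to 12 points at d = 0.5 and ρ = 0.5, and about 6 to 7 points against the change score at ρ = 0.7. These sizes rest on an assumed effect and correlation, complete data and a single post-intervention comparison. The direction does not: ANCOVA had the highest power in every setting tried. The low absolute power at d = 0.5 belongs to the sample size and is not part of this point. Result-driven covariate choice is a risk of selective modelling. The two lists of allocation factors contradict each other and must be reconciled before the first allocation.

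**What to change.** 1. Data Analysis and Handling Missing Data: replace the covariate sentence with, for example: *Each STAI subscale is compared between arms at the post-intervention visit by ANCOVA containing arm, the baseline score of that subscale as a continuous covariate, and the factors used to stratify allocation. Other covariates are used in sensitivity analyses only.* The equivalent mixed model over visits would also serve, provided that one of the two is named as primary before data are seen.
2. Procedure, Overview: state the stratification factors once, including which anxiety score is used and how it is cut.
3. Participant Recruitment: align the list with those factors, and report financial level and education type descriptively.

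Cost: a few sentences. All the variables are already collected, so no participants, visits or measurements are added. Items 2 and 3 have to be settled before the first participant is allocated. Item 1 can be settled at any time before outcome data are examined.

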### Ethical Considerations

This study has been approved by the University of Medicine and Pharmacy IRB Research Ethics Committee (466/2024-15.10) and will be conducted in full compliance with the Declaration of Helsinki, the World Medical Association’s ethical guidelines for human research, and relevant national and institutional research policies. These ethical safeguards ensure that participants’ rights, safety, and well-being are prioritized throughout the study.

Before enrollment, all participants will provide written informed consent, ensuring that they fully understand the study’s purpose, procedures, potential risks, and benefits. For participants aged <18 years, parental or legal guardian consent will also be required. The consent process will emphasize that participation is entirely voluntary, without compensation and individuals have the right to withdraw at any time without penalty or consequence. To maintain participant confidentiality, all collected data will be deidentified and coded, ensuring anonymity throughout the study. Data will be stored in secure, password-protected electronic databases, accessible only to authorized research personnel. Any publications or data-sharing initiatives will strictly follow ethical guidelines to prevent participant identification.

While both VR-CBT and yoga interventions are considered low risk, potential adverse effects will be monitored throughout the study. Participants will be encouraged to report any AEs immediately, and a clinical psychologist will be available to provide support as needed. Should a participant experience persistent distress or injury, they will be referred to appropriate medical or mental health services for further care. A structured protocol will be implemented for identifying, documenting, and managing AEs. Given the noninvasive nature of the interventions, a formal independent data monitoring committee is not required. Instead, a DSMB will be responsible for ensuring participant safety, protocol adherence, and data integrity. The DSMB will convene at predefined intervals (midstudy and at trial completion) to review participant retention, adherence, and safety outcomes. Findings will be documented and reported as needed. Any protocol deviations or concerns will be escalated to the PI and the IRB, with corrective actions implemented as necessary.

### Dissemination Policy

To ensure transparency and broad dissemination of trial findings, the study results will be communicated through multiple channels to participants, health care professionals, researchers, and the public. Upon study completion, participants will receive a summary of findings in lay language, detailing overall outcomes without compromising confidentiality. Results will also be submitted for publication in peer-reviewed journals and presented at academic conferences, mental health symposiums, and relevant professional meetings. In addition, findings will be reported in public clinical trial registries, such as ClinicalTrials.gov, in accordance with international reporting standards. The research team will explore open-access publication options to maximize accessibility. Where feasible, deidentified data may be shared upon request with other researchers for secondary analysis, following institutional guidelines on ethical data sharing. Any publication restrictions will be governed by funding agreements, journal policies, and ethical considerations, but the investigators and sponsors affirm their commitment to full, unbiased reporting of results, regardless of outcome.

Authorship for all study-related publications will follow the guidelines set forth by the International Committee of Medical Journal Editors, ensuring that all listed authors meet the criteria for substantial contributions to the study. Specifically, authorship will be granted to individuals who have (1) significantly contributed to the study design, data collection, analysis, or interpretation; (2) participated in drafting or revising the manuscript critically for intellectual content; and (3) approved the final version for publication. Individuals who contribute to the study but do not meet all authorship criteria, such as those providing administrative support, technical assistance, or general supervision, will be acknowledged in the acknowledgments section rather than listed as authors. The use of professional medical writers is not planned for this trial.

To promote transparency and reproducibility, the study team intends to provide public access to key study materials, including the full trial protocol, anonymized participant-level dataset, and statistical analysis code, where feasible and ethically appropriate. The final protocol will be made available through an open-access repository or as a supplementary file in peer-reviewed publications. Requests will be reviewed by the study’s ethics board and PI, ensuring that data align with ethical guidelines and data protection laws. In addition, the statistical code used for data analysis will be deposited in a publicly accessible repository (eg, GitHub and Open Science Framework) to facilitate replication and secondary analyses. Restrictions may apply if the data contain sensitive information that cannot be fully anonymized. Further details on data access and sharing policies will be outlined in the final study report and registered in public trial databases, such as ClinicalTrials.gov.

## Results

This study hypothesizes that the implementation of both VR techniques and yoga practices will yield a significant reduction in anxiety symptoms, as measured by the STAI-Y1 and STAI-Y2 scales. This study will start in the middle of the academic year in the fall of 2025 (to be relevant for performance anxiety) and will end in June 2026. It is anticipated that the VR group will experience a decrease in performance anxiety symptoms compared to the yoga group, which may require additional sessions. Concurrently, yoga sessions are expected to exert an intense impact with substantial psychoemotional rehabilitation effects. Furthermore, both interventions are predicted to lead to a meaningful enhancement in emotional regulation abilities, as assessed by the Emotion Regulation Questionnaire, with participants engaged in yoga anticipated to develop more effective cognitive reappraisal strategies. In assessing QoL, the use of the QoL Inventory among participants aims to reveal improvements, particularly in areas related to academic stress and examination-related anxiety, with both groups likely to report enhanced QoL after the intervention.

Comparative analyses between the 2 groups will highlight the specific outcomes associated with each technique. It is expected that the VR intervention may offer a more significant advantage in reducing acute anxiety symptoms, with rapid effects on stress perception. At the same time, the yoga group may sustain these effects over the long term by learning self-regulation methods. Neurobiological measurements are projected to provide evidence of favorable modifications in autonomic nervous system functioning, indicating beneficial biological responses to anxiety in both intervention groups. In addition, postintervention evaluations will reflect increased participant satisfaction with the techniques, particularly noting subjective differences in comfort and effectiveness. Yoga techniques are anticipated to be perceived as more relaxing, whereas VR may be seen as more stimulating.

In summary, the expected outcomes involve a reduction in anxiety symptoms, enhancement of life quality, and adaptation of emotional regulation strategies, underscoring the efficacy of both intervention methods in addressing performance anxiety among young individuals. This research may significantly contribute to the mental health field by providing relevant data for effective therapeutic strategies and new avenues of study.

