The participants will then start the psychoemotional support program and complete an anxiety level assessment at the end of each intervention session. At the end of the program, participants will complete the anxiety questionnaire again, along with an instrument assessing their comfort, discomfort, and the quality of the specific intervention techniques. To evaluate manifestations of performance anxiety, correlations between clinical anxiety and academic anxiety will be checked to indicate the strength and significance of their relationship. Details about the implementation of the techniques are presented in Table 1.

**Table 1 table1:** Overview of intervention components for virtual reality (VR)–assisted cognitive behavioral therapy (VR-CBT) and yoga-based interventions.

Intervention and phase		Session components	Duration

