**VR-CBT**			
	Introduction and familiarization (sessions 1-2)	Psychoeducation, familiarization with VR equipment, and guided relaxation exercises	20-30 min per session
	Active exposure (sessions 3-8)	Exposure to anxiety-inducing VR scenarios (eg, virtual presentations), cognitive restructuring, and relaxation	20-30 min per session
	Evaluation and feedback (session 9)	Review of selected VR scenario, QoLI^a^, debriefing, and feedback	20-30 min

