**Yoga-based intervention**			
	Yoga practices (sessions 1-10)	Body postures (asanas), breathing techniques (pranayama), meditation, and relaxation exercises	60-90 min per session
	Final assessment (after the intervention)	QoLI, and self-report feedback on intervention experience	60 min

^a^QoLI: Quality of Life Inventory.

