### VR Cognitive Behavioral Intervention and Theoretical Background

The psychoemotional support intervention, facilitated by VR exposure techniques (6-10 sessions), uses Guided Meditation VR software and stand-alone Oculus Quest 2 and HTC Vive Flow hardware for alleviating performance anxiety. These consist of approximately 6 to 10 sessions of 20 to 30 minutes each of psychoemotional support based on cognitive behavioral techniques and integrative psychotherapy (with extension to a maximum of 1 h, if necessary). They will be carried out over a period of 2 weeks, up to a maximum of 1 month if it is not possible to organize the sessions in optimal conditions. After 1 month, the participants are reported as having withdrawn (in case of a request from the participants) or dropped out of the psychoemotional support program. The initial sessions (1-2 sessions) are designed for psychological assessment, psychoeducation, and familiarization with VR exposure techniques. In the next 2 to 3 sessions, different VR scenarios are tested to find a comfortable virtual environment for each patient. We test if patients agree that they are present in that generated virtual environment in a manner comparable to exposure in a natural environment (eg, a walk by the beach, in a forest, or an underwater itinerary). At this stage, subsequent exposure techniques will be developed using a combination of cognitive restructuring and relaxation methods, aimed at familiarizing participants with the technology and ensuring a pleasant experience. The next 1 to 2 sessions will continue with exercises already chosen, based on cognitive restructuring techniques combined with relaxation techniques. The last session is designed to review one of the exercises, assessing the quality of the technique and offering suggestions for improvement by going through a set of questions (eg, QoL through the QoL questionnaire). Each session concludes with a brief clinical assessment of anxiety using the State-Trait Anxiety Inventory (STAI) tool. Specific manifestations of performance anxiety are assessed.

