### Yoga Intervention and Theoretical Background

This psychoemotional assistance intervention is facilitated through breathing techniques, meditation, and body postures (yoga). The program is designed to reduce anxiety and improve emotional well-being through a holistic mind-body approach. This program is a psychoemotional support intervention that incorporates yoga-based techniques, including breathing exercises, meditation, and body postures. The program runs for 2 to 4 weeks, depending on the scheduling of the sessions, with participants attending 6 to 10 sessions lasting 60 to 90 minutes each. If participants do not complete the program within 1 month, they are considered to have withdrawn.

The sessions include the following:

Body postures (asanas) that include a sequence of yoga postures such as Tadasana (mountain pose); Surya Namaskar (sun salutation); and various standing and seated poses such as the tree pose, warrior pose, and triangle pose, aimed at promoting physical alignment and relaxation.Breathing techniques (pranayama) that include exercises to control and expand the breath, such as Bhastrika (bellows breathing), Ujjayi (victorious breathing), and specific breath locks (Bandhas) to regulate energy flow.Meditation and relaxation that includes techniques such as Shavasana (relaxation pose) and chanting of the AUM mantra promote mental calmness and relaxation.

As described in Patanjali’s Yoga Sutras, Yama and Niyama represent 2 fundamental sets of ethical and moral rules within the yoga system. These principles, which form the foundation of any practitioner’s spiritual evolution, are intended for advanced yoga practitioners and beginners. Patanjali structured the yoga system into 8 progressive stages, known as ashtanga, which include Yama (rules for interacting with others) and Niyama (rules of inner discipline) as the first 2 steps of this system. Essentially, Yama and Niyama aim to guide the practitioner toward moral and spiritual balance, regulating both external and internal behavior. Following these principles is vital for reducing negative influences that may affect the practitioner, thus hindering spiritual growth and mental calm.

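### Session counts conflict, nothing fixes when a participant's program ends, and the post-treatment STAI is tied to that unfixed end

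*Protocol article*

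**What the plan says.** **Session count.** The VR section states: "These consist of approximately 6 to 10 sessions of 20 to 30 minutes each". The yoga section states: "participants attending 6 to 10 sessions lasting 60 to 90 minutes each". Table 1 has fixed counts instead. Its VR-CBT block closes with "Evaluation and feedback (session 9", and its yoga block reads "Yoga practices (sessions 1-10".

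**Program length.** VR-CBT is planned over 2 weeks, up to 1 month if sessions cannot be organised well. Yoga runs 2 to 4 weeks depending on scheduling. Participants who go beyond 1 month are classed as withdrawn (yoga), or as withdrawn or dropped out (VR-CBT).

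**Scoring.** Under Procedure, Overview, participants "complete an anxiety level assessment at the end of each intervention session". The VR section names the STAI for this, which is also the primary instrument in the Abstract. The post-treatment measurement is set as follows: "At the end of the program, participants will complete the anxiety questionnaire again". The Abstract also mentions follow-up assessments, without giving their timing.

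**Blinding.** The Blinding section covers outcome assessors and data analysts. It does not cover those who run the sessions.

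**Reasons for variation.** The Results section expects faster benefit from VR "compared to the yoga group, which may require additional sessions". Sample Size Determination argues that "a smaller population allows for more efficient adaptation of the intervention to individual needs".

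**The concern.** Three features meet here: an open number of sessions, a score on the primary instrument after each one, and an endpoint located at whichever session turns out to be last. The stated reasons for variation (scheduling and organisation) explain calendar length. They do not explain why one participant would have 6 sessions and another 10.

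Two things are at stake. The first needs no assumption about behaviour: the post-treatment STAI falls at different times from randomisation for different participants, and could do so systematically by arm, because the protocol itself expects yoga to need more sessions. A trial that contrasts a fast effect with a slow one is sensitive to when it measures. The second is conditional: if whoever ends the program can see the session scores and lets them influence the decision, the last score is selected for being low.

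**Working it through.** **1. Do the session counts agree?**

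| Source | VR-CBT | Yoga |
|---|---|---|
| Intervention sections | 6–10 | 6–10 |
| Table 1 | 9 | 10 |
| VR phases in the text: (1–2) + (2–3) + (1–2) + 1 | 5–8 | – |

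The lower sum is 1 + 2 + 1 + 1 = 5 and the upper is 2 + 3 + 2 + 1 = 8. The VR arm thus has three descriptions that disagree and the yoga arm has two.

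**2. When is the endpoint taken?** At program end, so between about 2 weeks and 1 month after the start. No time from randomisation is stated.

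**3. Scale.** The plan's 30 per group (80% power, 5% level) cannot be reproduced, because no effect size or SD is given. Solving backwards with a two-sided test: d = (1.960 + 0.842) × √(2/30) = 2.802 × 0.258 = 0.72. The exact t-test gives 0.74.

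**4. What if stopping followed the score?** This is a simulation under assumptions that are not in the protocol:
- There is no true effect and no time trend, and the total SD is 1.
- Score = stable person component + independent session noise, with correlation ρ between a person's scores.
- The program stops at the first of sessions 6 to 10 with a good score, otherwise at 10.
- The score that triggers stopping is also the endpoint.

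Spurious within-arm reduction from baseline, in SD:

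| ρ | Stop at or below the mean | Stop 0.5 SD below the mean | Stop 0.5 SD below own baseline |
|---|---|---|---|
| 0.3 | 0.55 | 0.60 | 0.50 |
| 0.5 | 0.40 | 0.41 | 0.42 |
| 0.7 | 0.24 | 0.24 | 0.31 |
| 0.85 | 0.12 | 0.12 | 0.19 |

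A within-arm test at n = 30 (first and third rules) is then falsely significant in about 39 to 77% of trials for ρ from 0.7 to 0.3.

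**5. Does this reach the between-arm comparison?** With 30 per arm and change from baseline as outcome:
- Same rule in both arms: bias about 0, type I error 4.7 to 5.1%.
- Rule in one arm only, the other always having 10 sessions, ρ from 0.7 to 0.3: bias 0.24 to 0.55 SD, type I error about 23 to 45%. Comparing final scores instead of change gives about 17 to 64%. This is a worst case.
- Endpoint is a fresh score, independent of the one that triggered stopping: bias about 0 and type I error about 5%, within and between arms.
- Stop triggered by the preceding session, endpoint at the next: bias about 0 with independent noise. With an assumed carry-over of 0.5 between adjacent sessions, about 0.04 to 0.19 SD remains.

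**The case against.** A reader might infer that the protocol lets facilitators stop once a participant scores well, and that the trial therefore has a false-positive rate of 17 to 64%. The documents do not support that. No passage links program end to a score. The only stated drivers of length are logistical. The remark about additional yoga sessions is an arm-level expectation among anticipated findings, and the remark about individual needs is a sample-size argument that mentions neither session count nor STAI.

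The described schedule also works against the mechanism. The last VR session is a planned review, and the procedure separates the per-session assessment from the questionnaire at program end. If the decision to finish comes before the final score exists, the bias largely disappears. The worst case further requires flexible VR against fixed yoga, whereas the text gives both arms the same range and Table 1 fixes both. Finally, an article may leave session-completion rules to a fuller protocol.

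Most of this stands, and it limits the claim. It does not remove three things. The session counts contradict each other on the page. The endpoint is expressly placed at program end, which is a stated choice and not an omitted detail. And the within-arm reductions, which the Results section hypothesises for both interventions, have no between-arm cancellation to protect them. Follow-up assessments exist, but they have no stated time and do not repair the end-of-program score.

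**Conclusion.** The point holds in limited form. The session-count passages contradict each other, nothing states what ends a participant's program, and the post-treatment STAI moves with that end, so assessment time and treatment received can differ by participant and arm. That much follows from the text alone.

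Score-driven stopping is a possibility left open, not a planned rule. If it happened and the triggering score were the endpoint, within-arm reductions would be inflated by 0.12 to 0.60 SD. For scale, the trial has 80% power only for a between-arm difference of about 0.72 to 0.74 SD. Between-arm bias would need the arms to apply the rule differently. The sizes rest on assumed stopping rules and assumed correlations of 0.3 to 0.85; the protocol gives neither. The exposure should be closed before enrolment, but it is not evidence that the primary comparison is biased.

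**What to change.** 1. Reconcile the session counts across the two intervention sections, the VR phase description and Table 1. The sponsor chooses the number and the rule.
2. State that the decision to end a participant's program does not depend on session STAI scores, and withhold those scores from whoever makes it.
3. Take the primary STAI at one fixed time from randomisation for every participant in both arms, however many sessions were received, including those who stop early. This also gives a measurement time for participants classed as withdrawn at 1 month, which the intention-to-treat analysis needs.

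The cost is protocol and session-form wording. There is a small downside: some participants will complete the final questionnaire days after their last session, and there is less freedom to adjust program length in response to scores.
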